### Study population

Participants, aged 1–65 years in the US or 2–65 years outside the US, will be eligible to enroll if they fulfill the following key inclusion criteria: have a confirmed clinical diagnosis of TSC with a history of seizures in accordance with the 2012 International Tuberous Sclerosis Complex Consensus Conference criteria, which were updated in 2021 [13,25] and have behavioral problems—such as aggression, impulsivity, temper tantrum, self-injury, hyperactivity, extreme shyness, mood swings, poor eye contact, repetitive behaviors, restlessness, difficulty getting along with peers, and rigidity/inflexibility to procedure and/or change—that are considered moderate or severe according to the Caregiver Global Impression of Severity (CareGI-S) at screening. At baseline, prospective participants must have a most problematic behavior score of ≥6 on TAND-SQ to remain eligible. EpiCom participants must either be naive to CBD treatment or must have been off CBD treatment for ≥3 months before screening and taking ≥1 ASM at a stable dose. Concomitant ASMs are allowed, but any modifications or additions are to be avoided in the first 12 weeks, except changes permitted for participant safety reasons.

Prospective participants will be excluded from the study if they had any medical condition that in the investigator’s opinion could affect the study outcomes. This includes significant surgery for epilepsy that in the opinion of the investigator may impact the outcome’s assessment. In addition, participants will be excluded if they have initiation of felbamate within the year before screening, use recreational or medicinal cannabis or synthetic cannabinoid-based medications within the 3 months before screening and are unwilling to undergo a 1-month washout period before rescreening, have significant hepatic impairment, or have any history of suicidal behavior or any suicidal ideation.

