**TAND Outcomes**			
ABC [26,27] A caregiver-reported tool that allows for assessments of problematic behavior in children and adults with developmental disabilities Caregivers will rate the participant’s specific symptoms across the following subscales: irritability, social withdrawal, stereotypic behavior, hyperactive noncompliance, and inappropriate speech	Change from baseline at weeks 13, 26, and 52	Can be used for children and adults Used for assessment in diseases with behavioral problems, including ASD, Down syndrome, and fragile X syndrome [26,28,29] Widely used for evaluating treatment outcomes in autism [30,31,32]	10–15 min
TAND-SQ [19,20] A checklist completed by caregivers or adults^a^ with TSC for assessment of symptoms across TAND-related domains (i.e., neuropsychiatric, cognitive, and behavioral symptoms, psychosocial impact, and overall burden) that can be tracked over time The single most problematic behavior on TAND-SQ for each participant will be identified by the caregiver and the change over time in that behavior will be assessed using an 11-point Likert-type scale Changes in the TAND clusters (scholastic, neuropsychological, ASD-like, dysregulated behavior, overactive/impulsive, mood/anxiety, eat/sleep) and overall NRS TAND-related symptoms will also be evaluated in the study	Change from baseline at weeks 13, 26, and 52	Under validation as part of the TANDem project [21]	20–30 min
CBCL [33,34]/ABCL [35,36] Caregiver-reported questionnaires that examine internalizing behaviors (e.g., depression and anxiety), externalizing behaviors (e.g., aggression), stress, obsessive-compulsive behaviors, and “sluggish cognitive tempo” These questionnaires allow for an assessment of the participant’s behaviors on a 3-point Likert scale	Change from baseline at weeks 26 and 52	CBCL, ABCL, and ASR are components of ASEBA, a widely used and validated measure to assess behavioral, emotional, and social problems and adaptive functioning in individuals of all ages [37] Versions of the CBCL are validated in participants aged 1.5–5 years and 6–18 years CBCL was found to not be as effective as the TAND checklist in detecting neuropsychiatric and psychopathological problems associated with TSC [34] ABCL is validated in participants aged 18–59 years; however, in the current study, it will be used for participants aged 18–65 years	15–20 min

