**Seizure Outcomes**			
The proportion of participants with ≥25%, ≥ 50%, ≥ 75%, and 100% reduction (responder rates) from baseline The proportion of participants experiencing a worsening, no change, or improvement in seizure frequency from baseline	Change from baseline in the proportion of participants with a response at each evaluable visit	—	—
Seizure-free days	Change from baseline in the number of seizure-free days at weeks 4, 13, 26, and 52		

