To assess effects on specific TAND domains, additional instruments will be included, such as the Patient-Reported Outcomes Measurement Information System (PROMIS), which uses latest advances in information technology, psychometrics, and health survey research to measure patient-reported outcomes, because of the increasing focus on moving toward the use of patient-centered assessment tools [38–40]; executive functioning outcomes evaluated using Behavior Rating Inventory of Executive Function (BRIEF) [41–43,45]; and sleep outcomes evaluated using Children’s Sleep Habits Questionnaire (CSHQ) [46–48] or Pittsburgh Sleep Quality Index (PSQI) [49–51]. Additionally, Pediatric Quality of Life Inventory (PedsQL) [52,53] and the PedsQL Family Impact Module (PedsQL FIM) [54,55] will be used to evaluate QoL and family functioning.

The analysis of TAND-related outcomes will be done in participants with and those without seizure responses to CBD treatment using TAND-SQ, CBCL/ABCL/ASR, BRIEF, PROMIS, CGI-S, and PGI-S/CareGI-S to explore the TAND outcomes independent of the effect of CBD treatment on seizure outcomes.

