### Statistical analysis

EpiCom is an exploratory study, so no formal statistical hypothesis will be tested. Ranking is not assigned to the study endpoints; therefore, no hierarchical testing strategy or other multiplicity adjustments will be considered. Given that the study is not controlled, no direct causal attribution of any observed association to CBD treatment will be made based on study findings. The study is not designed to distinguish whether improvements in TAND outcomes are due to CBD treatment or if they are the result of seizure reduction. A modelling approach will be used to explore the extent to which the observed associations of CBD treatment with TAND endpoints is associated with the change in seizure frequency during follow-up. Its marginal/causal effects may be further investigated with an exploratory mediation analysis [64].

Outcomes will be reported using standard descriptive statistics for continuous variables, including 95% CIs for the mean (including SD) or median (including the first and third quartiles, and the minimum and maximum values) change. Counts and percentages will be reported along with the 95% CI of the rate. Statistics will be presented overall and by age, where applicable. If provided, *P* values will be declared as nominal. An intermediate analysis at week 26 will be performed to describe any early trends.

A generalized linear mixed model (GLMM) will be used to evaluate the significant change from baseline to week 26 in effectiveness endpoints, adjusted by the assessment at baseline and age at baseline. During the second treatment period, summary statistics for endpoints may be computed for and between the CBD treatment and SoC arms. At week 52, a GLMM will be used to describe the association of treatment with change from baseline in effectiveness endpoints, adjusted by assessment at baseline, and a propensity score calculated based on age at baseline, sex, percentage change from baseline at week 26 in seizure frequency, 28-day average seizure-free days at week 26, and the number of concomitant ASMs. Least-squares means of the treatment effect (CBD vs SoC), two-tailed 95% CI and the unadjusted *P* values will be generated if at least 25% of the participants reaching the 26-week interim review will opt for SoC treatment in the second treatment period.

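### Antiseizure-drug changes after week 12 can enter both the week-26 behavioural change and the seizure-response strata, and the stated analyses do not separate them

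*Protocol article*

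**What the plan says.** **Background ASMs.** Under Study population, participants take at least one ASM at a stable dose, and "any modifications or additions are to be avoided in the first 12 weeks, except changes permitted for participant safety reasons". Nothing is said about changes after week 12, nor about when the 12 weeks begin. Medication changes are recorded in the eDiary throughout (Study endpoints, procedures, and assessments).

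**Week-26 model.** Under Statistical analysis, a generalized linear mixed model is used to "evaluate the significant change from baseline to week 26 in effectiveness endpoints, adjusted by the assessment at baseline and age at baseline". No ASM term is listed. The Discussion nevertheless says that the model deals with confounding.

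**Strata.** The TAND outcomes section analyses behaviour in "participants with and those without seizure responses to CBD treatment", with the aim of looking at behaviour apart from CBD's effect on seizures. Statistical analysis adds a model relating TAND change to seizure change, and possibly a mediation analysis.

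**Week 52.** The CBD versus standard-of-care comparison uses a propensity score built from age, sex, percentage change in seizure frequency at week 26, "28-day average seizure-free days at week 26, and the number of concomitant ASMs".

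**Assessment times.** Table 1 gives "Change from baseline at weeks 13, 26, and 52" for the Aberrant Behavior Checklist (ABC) and TAND-SQ, and "Change from baseline in the number of seizure-free days at weeks 4, 13, 26, and 52". Global impressions and retention also have a week-13 time. CBCL/ABCL/ASR and PROMIS are read at weeks 26 and 52 only; BRIEF, the sleep scales and both PedsQL scales at week 26 only.

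**The concern.** Everyone receives CBD up to week 26, so there is no concurrent group in which an effect of later ASM changes would cancel. Such an effect passes into the mean change.

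The strata are the sharper problem. Take a participant with no seizure benefit by week 12 who starts another ASM at week 14 and has 50% fewer seizures at week 26. By the label used, that person is a seizure responder to CBD. If the new drug also changes behaviour, for better or worse, that behavioural change is shown in the responder stratum. The analysis meant to look at behaviour apart from CBD's seizure effect then contains another drug's effect on both. The model of TAND change on seizure change, and any mediation analysis, share the weakness: a later ASM change can act on the mediator and on the outcome.

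**Working it through.** **1. The plan's own figure.** Evaluable at week 26: 60. Withdrawal: 20%. 60 / (1 − 0.20) = 75, the stated enrolment. It reproduces and is not in dispute.

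**2. Length of the uncovered period.** Assuming that the 12 weeks start with CBD:
- to week 26: 26 − 12 = 14 weeks; 14/26 = 54%
- to week 52: 52 − 12 = 40 weeks; 40/52 = 77%
- at week 13: 13 − 12 = 1 week

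If the count began at screening and the full 49 days (7 weeks) were used, 12 − 7 = 5 treated weeks would be covered, leaving 26 − 5 = 21 weeks, or 21/26 = 81%.

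**3. Precision at week 26.** In SD units of the change score, the 95% CI half-width is 1.96/√60 = 0.253.

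**4. Possible shift in the mean.** Let f be the share of participants who change ASMs between weeks 12 and 26, and d the resulting shift in their score, in SD. The mean change moves by f × d. Neither input is in the documents; both are assumptions, and d may have either sign. Absolute values:

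| f | d = 0.25 | d = 0.50 | d = 0.75 |
|---|---|---|---|
| 10% | 0.025 | 0.05 | 0.075 |
| 20% | 0.05 | 0.10 | 0.15 |
| 30% | 0.075 | 0.15 | 0.225 |
| 40% | 0.10 | 0.20 | 0.30 |

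Relative to the half-width, this runs from 0.025/0.253 = 0.1 to 0.30/0.253 = 1.2.

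**5. Why dropping changers is a poor remedy.** At f = 10%, 20%, 30% and 40%, 54, 48, 42 and 36 of the 60 would remain. At 36 the half-width is 1.96/√36 = 0.327. If those doing badly are the ones whose ASMs are changed, which is plausible but undocumented, removing them could also flatter the remaining mean.

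**6. Where week 13 helps.** The stratified analysis uses TAND-SQ, CBCL/ABCL/ASR, BRIEF, PROMIS and the global impressions. Only TAND-SQ and the global impressions have a week-13 reading. For the other instruments, ASM change has to be dealt with at week 26.

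**7. The week-52 score.** Replacing one ASM by another, or altering a dose, leaves the count the same. The time at which the count is taken is not stated. The two week-26 seizure terms pick up an ASM change in so far as it altered seizures, but not a direct effect on behaviour.

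**The case against.** The best case for the plan has five parts.

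- **The question asked.** CBD is added to standard of care in a study described as real-world. Later ASM changes can be seen as part of that care, and a stable-ASM result answers a different question. This stands as a reason to keep the planned week-26 analysis. It does not rescue a stratum labelled as response to CBD.
- **Exploratory status.** The article tests no formal hypothesis, says "Ranking is not assigned to the study endpoints", and disclaims causal attribution to CBD. This stands and limits the severity. Week 26 is the modelled and evaluability time point, not a declared primary readout.
- **Provisions already there.** Changes are recorded, week-13 results are planned, the week-52 score contains an ASM count and two week-26 seizure terms, and the Discussion allows for concomitant-medication subgroups. It would be wrong to say that no account is taken of ASM changes. But recording is not analysis, the subgroup work is not committed, and none of this reaches the week-26 model or the strata.
- **Detail left to the analysis plan.** Sensitivity analyses may well be in the SAP, which is not shown, and their absence here is no finding. The point rests on what the article does specify: the covariates, the strata and their label, the propensity terms, and the statement about confounding.
- **Direction.** A reader might infer that ASM changes inflate the week-26 results. The documents do not support that. A change may be a reduction or withdrawal, a new ASM may worsen behaviour, and the Introduction says data on any ASM improving TAND are limited. Nor do they say that ASMs may be changed freely after week 12; they are silent on that period.

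**Conclusion.** The point holds in a limited form. The ASM window ends well before week 26, and the week-26 model as stated has no term for later changes. The strata would credit CBD with seizure reduction that followed another drug, and the ASM count at week 52 misses swaps and dose changes. The Discussion's statement on confounding is not borne out at week 26, where age is the only covariate besides the baseline score.

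The 54% rests on the 12 weeks starting with CBD. The 0.025 to 0.30 SD range rests wholly on assumed f and d, and its sign is unknown. Most of that range lies inside one CI half-width. Severity is minor to moderate: interpretation of the week-26 and stratified results is affected, but the article makes no false efficacy claim.

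**What to change.** Leave the care rule as it is and change the analysis only:

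1. Report the share of participants with any ASM addition, switch, dose change or withdrawal before week 26, by type and timing.
2. Keep the planned week-26 analysis and add beside it a sensitivity analysis that accounts for ASM change without dropping those who changed. One way is to shift their week-26 scores by a range of assumed values in both directions and show when the conclusion alters.
3. In the seizure-response strata and the model of TAND change on seizure change, do not classify seizure reduction that first appears after an ASM change as response to CBD, or show the strata both ways.
4. Add any ASM change before the week-26 choice to the week-52 propensity score, and state when the ASM count is taken.
5. Identify the planned week-13 results as the near-stable-ASM readout for the endpoints measured then.
6. Reword the Discussion's statement on confounding to match the covariates actually listed.

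**Cost.** A few extra tables from data already recorded, smaller and less precise subsets, and possibly a lower seizure response rate. The propensity score gains a sixth covariate in a small sample. If 60 participants reach the week-26 review and the 25% threshold is just met, the standard-of-care group has 0.25 × 60 = 15 participants, so 15/6 = 2.5 per covariate in place of 15/5 = 3. If that is too thin, the new term could replace the ASM count.

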### Treatment

All patients will receive adjunctive CBD (Epidiolex^®^/Epidyolex^®^, 100 mg/mL oral solution) treatment at a starting dose of 2.5 mg/kg administered twice daily during the first week of the titration period. The dose will be increased to 10 mg/kg/d during the second week and may be increased further in weekly increments of 2.5 mg/kg, depending on each participant’s clinical response and tolerability, to a maximum dose of 25 mg/kg/d. The dose may be reduced at any time in case of intolerance to treatment; otherwise, a stable dosage will be maintained throughout the study.

### Study endpoints, procedures, and assessments

Participating caregivers are expected to complete most assessments. Adult participants or caregivers will record all participant/caregiver-reported assessments in an eDiary throughout the study; seizures, including episodes of status epilepticus; changes in participants’ health and concomitant medications, including the use of rescue medications; and inpatient hospitalization for epilepsy should be recorded. Participants and/or caregivers will be trained on how to record information (including the CareGI-S at screening) in the eDiary. The effectiveness evaluation will include both TAND-SQ and seizure-related endpoints (**Table 1**).

**Table 1 pone.0324648.t001:** Study assessments and endpoints.

Assessments/instruments	Endpoint	Description of instruments	
		Validation status	Time to complete the assessment
**TAND Outcomes**			
ABC [26,27] A caregiver-reported tool that allows for assessments of problematic behavior in children and adults with developmental disabilities Caregivers will rate the participant’s specific symptoms across the following subscales: irritability, social withdrawal, stereotypic behavior, hyperactive noncompliance, and inappropriate speech	Change from baseline at weeks 13, 26, and 52	Can be used for children and adults Used for assessment in diseases with behavioral problems, including ASD, Down syndrome, and fragile X syndrome [26,28,29] Widely used for evaluating treatment outcomes in autism [30,31,32]	10–15 min
TAND-SQ [19,20] A checklist completed by caregivers or adults^a^ with TSC for assessment of symptoms across TAND-related domains (i.e., neuropsychiatric, cognitive, and behavioral symptoms, psychosocial impact, and overall burden) that can be tracked over time The single most problematic behavior on TAND-SQ for each participant will be identified by the caregiver and the change over time in that behavior will be assessed using an 11-point Likert-type scale Changes in the TAND clusters (scholastic, neuropsychological, ASD-like, dysregulated behavior, overactive/impulsive, mood/anxiety, eat/sleep) and overall NRS TAND-related symptoms will also be evaluated in the study	Change from baseline at weeks 13, 26, and 52	Under validation as part of the TANDem project [21]	20–30 min
CBCL [33,34]/ABCL [35,36] Caregiver-reported questionnaires that examine internalizing behaviors (e.g., depression and anxiety), externalizing behaviors (e.g., aggression), stress, obsessive-compulsive behaviors, and “sluggish cognitive tempo” These questionnaires allow for an assessment of the participant’s behaviors on a 3-point Likert scale	Change from baseline at weeks 26 and 52	CBCL, ABCL, and ASR are components of ASEBA, a widely used and validated measure to assess behavioral, emotional, and social problems and adaptive functioning in individuals of all ages [37] Versions of the CBCL are validated in participants aged 1.5–5 years and 6–18 years CBCL was found to not be as effective as the TAND checklist in detecting neuropsychiatric and psychopathological problems associated with TSC [34] ABCL is validated in participants aged 18–59 years; however, in the current study, it will be used for participants aged 18–65 years	15–20 min
ASR^a^ [36] The ASR is a participant-reported version of the ABCL	Change from baseline at weeks 26 and 52	ASR is validated in participants aged 18–59 years; however, in the current study, it will be used for participants aged 18–65 years	15–20 min
PROMIS [38–40] Developed by the NIH as a collection of standardized outcome assessments for use in clinical studies This study will incorporate caregiver-assessed short-form PROMIS scales pertaining to the following domains: emotional distress (anger/irritability, anxiety), cognition, positive affect, and sleep disturbance	Change from baseline to weeks 26 and 52 in PROMIS domains	Can be used for children and adults Widely used and validated in large clinical trials [40]	≈5 min/questionnaire
BRIEF [41,42] A set of questionnaires to evaluate executive function from multiple perspectives Theoretically and statistically derived scales measure behavioral aspects such as the ability to control impulses, move freely between situations, modulate responses, anticipate future events, and monitor how an individual’s behavior impacts others BRIEF questionnaire will be completed by the caregiver	Change from baseline at week 26	BRIEF-P: validated for use in participants aged 2–5 years [43] BRIEF2: validated for use in individuals aged 6–18 years [44] BRIEF-A: validated for use in individuals aged >18 years [45] Questionnaires have been used in epilepsy studies and can be used with children who have developmental or acquired neurologic conditions such as learning disabilities, attention disorders, traumatic brain injury, lead exposure, pervasive developmental disorders, depression, and other developmental, neurologic, psychiatric, and medical conditions	10–15 min/ questionnaire
Abbreviated CSHQ [46,47] A caregiver-reported tool used to assess sleep habits and possible difficulties with sleep during the past week Includes items regarding bedtime habits, sleep behaviors, waking through the night, and morning wake-up	Change from baseline at week 26	Well-established sleep measure Validated in children 4–10 years and 2.5–5 years; has been used in children up to 12 years of age [48]	≈10 min
PSQI^a^ [49,50] A participant-reported tool that measures overall sleep quality across the following domains: subjective sleep quality, sleep latency, sleep duration, habitual sleep efficiency, sleep disturbances, use of sleep medicine, and daytime dysfunction during the past month Includes additional questions for the participant’s bed partner or roommate that are qualitatively assessed and do not contribute to the overall score	Change from baseline at week 26	Widely used screening tool for sleep dysfunction in nonclinical and clinical settings [51] Reliable and validated for use in individuals ≥18 years [51]	≈10 min
PedsQL [52] A questionnaire (caregiver-reported in this study) that assesses a participant’s QoL across physical, emotional, and social functioning, as well as functioning at school	Change from baseline to week 26	The PedsQL can be completed by children and young people, with versions available for people aged 5–7, 8–12, and 13–18 years; parent-rated versions are available for children aged 2–4, 5–7, 8–12, and 13–18 years It has been shown to be internally consistent and can distinguish between healthy children and those with health problems [53]	≈5 min
PedsQL FIM [54] A caregiver-reported scale that assesses the impact of pediatric chronic health conditions on parents/ guardians and the family Includes subscales that assess the impact on family daily activities and family relationships, as well as the parents’/guardians’ self-reported physical, emotional, social, and cognitive functioning, communication, and worry	Change from baseline to week 26	Preliminary reliability and validity demonstrated in families with children with complex health conditions [54] Shown to be a reliable and valid measure within a community sample [55]	≈10 min
